### Recruitment {15}

Approximately 15 UK head and oncology centres will recruit to the trial. Additionally, patient-facing material will be disseminated using social media and by circulating to head and neck oncology patient support networks, giving access to their nearest open centre.

## Assignment of interventions: allocation

### Sequence generation {16a}

Participants will be randomised to receive either arm A, standard supportive care (SSC), or arm B, PENTOCLO + SSC, (in a ratio of 1:1).

### Concealment mechanism {16b}

Participants and site staff will be unblinded as to allocation.

### Implementation {16c}

Participants will be randomised via a secure (24-h) web-based randomisation system controlled centrally by the trials centre. Randomisation lists will be generated in advance by a member of the trials unit team and will be stratified by study site using permuted blocks. This system is generated centrally by the trials unit using a computer algorithm and is concealed from the investigators and research teams/trial management group.

## Assignment of interventions: blinding

### Who will be blinded {17a}

Assessment of the primary endpoint is blinded, as de-identified clinical photographs and radiographs will be assessed by a remote, blinded, expert panel of assessors.

### Procedure for unblinding if needed {17b}

Not applicable, as participants and site staff will be unblinded.

## Data collection and management

### Plans for assessment and collection of outcomes {18a}

All data will be managed as per local Liverpool Clinical Trials Centre (LCTC) processes and in line with all relevant regulatory, ethical and legal obligations. The bespoke Case Report Forms (CRF) will be considered the source document for data where no prior record exists. A description of study instruments and classifications used are in the protocol available at the RAPTOR trial webpage. The CRFs are not available in a publishable form or document (and therefore cannot be appended or referenced) but details of their content are available by direct contact with the chief investigator.

### Plans to promote participant retention and complete follow-up {18b}

Retention of patients is encouraged by using 3-monthly trial visits, through telephone support by participating centres, and through prompting by use of the RAPTOR ePROM bespoke smartphone application. Discontinuation from trial intervention does not mean discontinuation of the study altogether, and the remaining study procedures, follow-up assessment/visits and data collection should be completed as indicated in the protocol (unless consent is specifically withdrawn). The exception for this is for surgical resection of ORN, and when this is performed, it will trigger a study completion visit irrespective of timepoint, as described above.

### Data management {19}

Data management procedures are described in detail in the protocol, available at the RAPTOR trial webpage [17].

### Confidentiality {27}

This trial will collect personal data (e.g. participant names), including special category personal data (i.e. participant medical information) and this will be handled in accordance with all applicable data protection legislation. This data will be handled confidentially and securely, and full details are within the protocol available at the RAPTOR trial webpage [17].

### Plans for collection, laboratory evaluation and storage of biological specimens for genetic or molecular analysis in this trial/future use {33}

In addition to the participant’s other blood samples, one blood sample is collected at the screening appointment, and stored by LCTC. The purpose of the sample is to create a bioresource for subsequent radiogenomic studies. The translational aspects of the study are exploratory and are not included in the trial endpoints. The translational work will be subject to the translational study report and not be part of the RAPTOR trial analysis plan.

## Statistical methods

### Statistical methods for primary and secondary outcomes {20a}

The primary outcome is time to healing. Healing rates will be estimated using the method of Kaplan and Meier. Comparisons across treatment groups will be performed using a log-rank test. Further analysis adjusting for key demographic and clinical covariates will be performed using a Cox proportional hazards model. The primary analysis will be carried out on the full analysis set, which will be defined on the intention to treat principle, retaining patients in their initially randomised groups irrespective of any protocol violations. Analysis of the primary outcome will be assessed using 1-tailed 0.1 level, as is consistent with the type I alpha level used in the study design. The one-sided test is employed in order to limit sample size and in the light of previous systematic reviews where no detriment to healing from PENTOCLO has been reported. All analyses of secondary outcomes will use the nominal *p* < 0.05 level to determine statistical significance. Full details of all planned analyses will be specified in a statistical analysis plan, which is provided as Appendix 1 (supplementary data).

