### Sample size {14}

Literature-based estimates of the use of PENTOCLO give a 12-month healing rate of approximately 60% and it is considered that this would have to demonstrate an improvement over a 40% rate in the control arm (equivalent to a hazard ratio of 0.56). Using a one-sided alpha level of 0.1 and a power of 90%, then a total of 78 events are required. Including a 5% rate for patient attrition and based on estimated recruitment rates, it is anticipated that 120 patients are required to obtain the events required.

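### Randomisation is stratified by site alone, but the stated primary log-rank test does not use site; if healing differs materially between sites, an unstratified test is conservative and gives away power

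*Protocol article*

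**What the plan says.** Under Implementation {16c}, the randomisation lists "will be stratified by study site using permuted blocks"; no other stratification factor is named. Under Recruitment {15}, "Approximately 15 UK head and oncology centres will recruit to the trial". With the planned 120 patients, that averages 120 / 15 = 8 per site.

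Under Statistical methods {20a}, the primary comparison of time to healing is stated as: "Comparisons across treatment groups will be performed using a log-rank test". The level is also fixed there: "Analysis of the primary outcome will be assessed using 1-tailed 0.1 level". Adjustment is confined to a further Cox analysis on key demographic and clinical covariates, with no mention of site. Full details are deferred to a statistical analysis plan (SAP, Appendix 1), which is not available here.

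Under Sample size {14}, the design contrasts 60% healing at 12 months on PENTOCLO with 40% in the control arm, "equivalent to a hazard ratio of 0.56". It continues: "Using a one-sided alpha level of 0.1 and a power of 90%, then a total of 78 events are required". The article gives no figure for variation in healing between sites.

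**The concern.** Permuted blocks within site force the arms to be nearly balanced at each site. If site predicts healing, the treatment difference then varies less from one randomisation to the next than an unstratified log-rank variance assumes. The test statistic is too small on average, the test runs below its nominal level, and power is lost. Pooling patients with different underlying hazards also dilutes the treatment effect that the test sees.

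Site differences are plausible in this trial. Under Intervention description {11a}, supportive care in both arms is partly left to the site clinician, and outpatient debridement is allowed. Under Outcomes {12}, a clinical indication for resection leads to censoring.

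What is at stake is efficiency and a match between the primary p-value and the allocation scheme. Falsely declaring PENTOCLO effective is not the risk.

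**Working it through.** **1. The plan's own figure.** From the stated rates, HR = ln 0.6 / ln 0.4 = 0.5575, which rounds to the stated 0.56. Schoenfeld's formula for 1:1 allocation, one-sided alpha 0.10 and 90% power is

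events = 4 (z₀.₉₀ + z₀.₉₀)² / (ln HR)² = 4 × (1.2816 + 1.2816)² / (ln HR)².

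This gives 78.2 for HR 0.56 and 77.0 for HR 0.5575. The stated 78 events are reproduced, using a formula for an unstratified comparison.

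**2. Events likely by 12 months.** 120 × 0.95 × (0.40 + 0.60)/2 = 57. Schoenfeld power with 57 events and HR 0.56 is about 82%. This shortfall is a separate issue. It matters here only as the baseline for the power figures below.

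**3. Simulation of the level and power.**
- From the article: 120 patients, 15 sites, 1:1 permuted blocks within site, 5% attrition, control healing 40% at 12 months, 3-monthly visits, one-sided 0.10. The within-site healing hazard ratio is 1 / 0.5575 = 1.79.
- Assumed: block size 4, site sizes equal or skewed, and normal site effects on the log hazard with SD 0 to 1.0.
- There were 4,000 trials per scenario. The Monte Carlo standard error is about 0.005 for the level and √(0.8 × 0.2 / 4000) = 0.006 for power.

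Results are shown as equal / skewed site sizes. Stratified here means every site is its own stratum.

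| Site SD | Level, unstratified | Power, unstratified | Power, stratified |
|---|---|---|---|
| 0 | 0.103 / 0.102 | 0.824 / 0.827 | 0.809 / 0.812 |
| 0.3 | 0.107 / 0.095 | 0.810 / 0.814 | 0.806 / 0.803 |
| 0.5 | 0.095 / 0.092 | 0.790 / 0.793 | 0.805 / 0.794 |
| 0.8 | 0.074 / 0.070 | 0.726 / 0.729 | 0.784 / 0.784 |
| 1.0 | 0.069 / 0.075 | 0.684 / 0.671 | 0.782 / 0.760 |

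The stratified test keeps its level (0.09 to 0.11) at every SD. Full stratification costs 1.5 points at SD 0 (0.824 − 0.809). It gains 5.8 points at SD 0.8 (0.784 − 0.726) and 9.8 at SD 1.0 (0.782 − 0.684) with equal sites. With follow-up stretched to 20 months, so that about 74 to 80 events accrue, the pattern is the same: 0.913 against 0.889 at SD 0, and 0.794 against 0.849 at SD 0.8.

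**4. Pooling small sites.** Many of the 15 sites will be small, so the practical version puts sites with fewer than 8 participants into one stratum. In simulation with unequal sites, this costs about 1 point at SD 0 (for example 84.5% unstratified, 83.8% pooled and 82.4% fully stratified). It is about equal or up to 2 points better at SD 0.5, and gains about 3 to 8 points at SD 0.8 to 1.0. In those runs the unstratified level at SD 0.8 to 1.0 was about 0.07 to 0.085.

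**5. What the SD means.** Suppose the median control site heals 40% by 12 months. A site u above the median on the log-hazard scale heals 1 − 0.6^exp(u).

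| Site SD | Healing one SD below and above the median site |
|---|---|
| 0.5 | 27% to 57% |
| 0.8 | 21% to 68% |
| 1.0 | 17% to 75% |

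**The case against.** The strongest objection is that the article does not say the test is unstratified. It names a log-rank test and sends the reader to an SAP for detail, and stratification and pooling rules are often found there. Site-stratified allocation and a log-rank test do not contradict each other. This stands to the extent that the fix must be conditional on what the SAP says. It does not remove the point, because the article describes both the primary test and its adjusted companion, and the sole randomisation stratum is in neither.

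Second, material harm appears only at an SD of about 0.8 or more, which means very different sites (step 5), and nothing in the article shows such a spread. This also stands. A reader might infer that forced balance by itself puts the test below 0.10. It does not: at SD 0 to 0.3 the level is 0.10 within simulation error, and at SD 0.5 it is 0.092 to 0.095.

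Third, a reader might infer that using site would bring the trial to its stated power. Simulated power of 88.7% and 92.4% for the pooled test (SD 0.8 and 1.0) can be obtained, but only by fixing the 40% and 60% healing rates averaged over sites. That implies a within-site effect larger than the stated hazard ratio. With the within-site effect held at the design value, fully stratified power at 12 months is 0.76 to 0.81.

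Finally, the pooling threshold is a matter of judgement. With an average of 8 per site, a cut at 8 could pool many sites and give back part of the gain. That is fair, and the threshold below is offered as an example.

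**Conclusion.** The point holds in a conditional form. As described in the article, the primary analysis does not use the only factor on which randomisation is stratified. If it is run that way and the site log-hazard SD is about 0.8 or more, the true level is about 0.07 to 0.085 instead of 0.10, and about 3 to 8 points of power are lost against a stratified test with small sites pooled. At SD 0.5 or below the choice makes little difference.

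These sizes rest on assumed values for the between-site SD, the site sizes and the block size. Any error is conservative and creates no bias towards PENTOCLO. This is a cheap improvement to an analysis that is valid but possibly inefficient. It is not a flaw that threatens the trial's conclusion.

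**What to change.** First check the SAP. If it already stratifies the primary test by site, one clarifying phrase in Statistical methods {20a} is enough. If it does not:

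- Make the primary test a log-rank stratified by study site, with small sites pooled into one stratum by a rule fixed before database lock (for example, fewer than 8 participants).
- Take the hazard ratio from a Cox model stratified in the same way.
- Keep the unstratified log-rank as a sensitivity analysis.

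The cost is wording in the protocol and SAP, plus about 1 point of power if sites do not differ at all (about 2 points if every site is kept as its own stratum). The choice can change the primary p-value, so it should be settled before outcome data by arm are seen. It adds no events, so the gap between 57 expected and 78 required events has to be dealt with separately.

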### Interim analyses {21b}

Interim analyses are not planned.

### Methods for additional analyses (e.g. subgroup analyses) {20b}

Additional or subgroup analyses are not planned, save for analysis of the patient preference phase, which will be largely descriptive and will be considered separately from the primary endpoint, as it is non-randomised data.

### Methods in analysis to handle protocol non-adherence and any statistical methods to handle missing data {20c}

Missing data are expected to be minor, and final analyses are planned to be carried out on a complete case basis. As much information as possible will be collected about the reasons for missing outcome data; this will be used to inform any imputation approaches employed in the analysis. If substantial missing data (> 10%) are observed and it is considered appropriate upon review, then multiple imputation using chained equations will be applied.

### Plans to give access to the full protocol, participant-level data and statistical code {31c}

The full protocol and analysis plan is available at the RAPTOR trial webpage [17]. All participant-level data will be published in the main trial report.

## Oversight and monitoring

### Composition of the coordinating centre and trial steering committee {5d}

#### Trial Management Group (TMG)

The TMG comprises the chief investigator, other lead investigators (clinical and non-clinical), patient representative, and members of the LCTC. The TMG will be responsible for the day-to-day running and management of the trial and will meet at least three times per year.

#### Trial Steering Committee (TSC)

The Trial Steering Committee will consist of an independent chairperson, other independent experts in the field of oral cancer, a statistician and at least one patient.

representative. The role of the TSC is to provide overall supervision for the trial and provide advice through its independent Chairman. The ultimate decision for the continuation of the trial lies with the TSC.

### Composition of the data monitoring committee, its role and reporting structure {21a}

#### Independent Data and Safety Monitoring Committee (IDSMC)

The Independent Data and Safety Monitoring Committee (IDSMC) consists of an independent chairperson in a related area of expertise, plus 2 independent members, one of whom is also an expert in a related area and another who is an expert in medical statistics. The IDSMC, which is constituted according to a published charter within guidelines established by the funder (NIHR) will be responsible for reviewing and assessing recruitment, interim monitoring of safety and effectiveness, trial conduct and external data. The IDSMC was convened before the trial opened to recruitment and will then define the frequency of subsequent meetings (at least annually). The IDSMC will provide a recommendation to the TSC concerning the continuation of the study.

### Adverse event reporting and harms {22}

Adverse events will be reported up to the point of primary endpoint and continued for patients remaining within patient preference phase. All nonserious adverse events (AE)/adverse reactions (AR), whether expected or not, will be recorded in the relevant page of the case report form. Serious adverse reactions (SARs), serious adverse events (SAEs) and suspected unexpected serious adverse reactions (SUSARs) should be reported within 24 h of the local site becoming aware of the event. Further details over the trial procedures pertaining to SAE, SAR and SUSARs are provided in detail in the RAPTOR protocol, available at the RAPTOR trial webpage [17].

### Frequency and plans for auditing trial conduct {23}

Monitoring is conducted to ensure protection of patients participating in the trial and all aspects of the trial (procedures, laboratory, trial intervention administration and data collection) are of high quality and conducted in accordance with sponsor and regulatory requirements. A detailed Trial Monitoring Plan is detailed within the full protocol available at RAPTOR trial webpage [17].

### Plans for communicating important protocol amendments to relevant parties (e.g. trial participants, ethical committees) {25}

Amendments to the trial protocol will be cascaded to all sites and trial investigators after appropriate ethical and regulatory approvals. Where relevant, amendments will additionally be communicated to trial participants. A chronology of protocol amendments is detailed in the relevant section of the protocol.

### Dissemination plans {31a}

The results from different participating sites will be analysed together and published as soon as possible. The findings of the trial will be summarised on the study web pages. Additionally, summaries of the main findings, in plain English form, will be provided to trial participants. The results generated from this Phase II trial may be used to guide the design and requirement for a subsequent phase III trial.

## Trial status

The RAPTOR trial is open and recruiting. The current Protocol Version Number is Protocol V4.1 18/10/2024). Recruitment began on 27/4/2023 and the study is expected to complete in 2027.

## Data Availability

Data will be published as soon as a possible and made available publicly. There are no contractual limitations on the availability of data to investigators.

## Abbreviations

RAPTOR: Randomised Controlled Trial of PENTOCLO in Mandibular Osteoradionecrosis
PENTOCLO: Drug combination: pentoxifylline, tocopherol and sodium clodronate
ORN: Osteoradionecrosis
ePROM: Electronic patient-reported outcome measure
OPT: Orthopantomogram (jaw x-ray)
LCTC: Liverpool Clinical Trials Centre
REC: Research ethics committee
IRAS: Integrated Research Application System
NIHR: National Institute for Health and Care Research
